### 4.8. Collection, Evaluation and Storage of Blood Samples

A total of three blood samples were collected from each participant during the study. At each appointment, 5 cc of blood was drawn, with 2 cc designated for immediate evaluations. The remaining 3 cc was processed to separate the plasma, which was stored as a reserve for potential future analyses. 

To enhance the accuracy of laboratory measurements, the 2-cc blood samples from all participants were stored in a freezer at -22°C. After the final sample was collected from the last participant, all samples were analyzed together by a single operator using the same device and kit. At the end of each day, the 3-cc reserve samples were transferred directly to a -80°C freezer for long-term storage. 

### 4.9. Subgroup Analyses

Subgroup analyses were conducted to evaluate differences between male and female participants, as well as between two BMI categories (25 - 30 kg/m² and >30 kg/m²). Differences in BMI were adjusted for fat-free mass (FFM).

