#### 3.2.2. Eligibility Criteria

##### 3.2.2.1. Inclusion Criteria

The study enrolled 30 adult participants aged 18 - 65 years diagnosed with overweight or obesity, defined by a BMI range of 25 - 40. Eligible participants had not experienced weight changes exceeding 5% in the past three months. Additionally, they had not taken any medications or followed dietary interventions aimed at weight loss within the last 3 - 6 months. Participants were required to refrain from engaging in intense physical activity and were not professional athletes (MET-min < 600 min/week).

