### 3.3. Sample Size

Due to the novelty of our study and the absence of prior similar research, the sample size was determined based on the study by Soares et al. (12). The respiratory exchange ratio was selected as the main variable, with the alpha error set at 0.05 and the beta error at 0.2. The sample size was calculated using the two-mean test formula for a quantitative trait in two independent groups. To account for potential attrition, the final sample size was determined to be 30 participants.

$$n=\frac{{\left(Z_{1-\frac{\alpha }{2}}+Z_{1-\beta }\right)}^{2}\left(\sigma_{1}^{2}+\sigma_{2}^{2}\right)}{{\left(\mu_{1}-\mu_{2}\right)}^{2}}$$

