### 4.1. Assignment of Interventions: Allocation Sequence Generation

This randomization was conducted using a simple randomization technique to allocate participants in a 1:1 ratio to one of two sequence groups: Sequence 1, where participants received meal A in the first week and meal B in the second week; and sequence 2, where participants received meal B in the first week and meal A in the second week. Fifteen participants were allocated to each sequence group. 

The random number table was used to generate the allocation sequence. To ensure allocation concealment, an independent individual not affiliated with the study placed the random sequence into opaque, sealed envelopes. At baseline, each participant randomly selected one envelope, and the sequence inside determined the order in which they received the meals. Additionally, participants were blinded to the order of meal administration. Meals were prepared in advance to appear as identical as possible, with minimal distinguishing features, so that participants did not know which diet they were receiving at any stage. Standardization emphasized uniform meal presentation with minimal features to maintain participant blinding to the meal order. 

This study was a randomized controlled trial employing a crossover design and involving a total of 30 participants (15 women and 15 men). During the first phase, each participant received one of the two meal interventions: Either an HP-HF-LC meal or an HP-LF-HC meal. In the second phase, participants received the alternate meal. Due to the crossover design and the differences in food components between phases, blinding was feasible only for the sequence groups. 

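### BMI is examined only as 25-30 versus >30 kg/m²; if the meal effect changes roughly linearly with BMI, this cut loses about a third to a half of the BMI information in a secondary analysis of 30 people

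*Protocol article*

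**What the plan says.** Section 3.2.2.1 of the protocol article admits adults with overweight or obesity, "defined by a BMI range of 25 - 40". Section 4.5.4 measures height to 1 mm and weight to 100 g, so BMI is known almost exactly for everyone.

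Section 4.9 plans subgroup analyses of "differences between male and female participants, as well as between two BMI categories", the latter being "two BMI categories (25 - 30 kg/m² and >30 kg/m²"). It adds one further sentence: "Differences in BMI were adjusted for fat-free mass (FFM"). No section describes BMI as a continuous modifier of the meal effect.

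On size, section 3.3 states that "the final sample size was determined to be 30 participants". Section 4.1 fixes the sex split, "involving a total of 30 participants (15 women and 15 men"), but no section states a balance across the BMI cut. Under section 3.1 every participant eats both meals, so each person yields a within-person meal difference.

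**The concern.** With the cut, participants at 29.9 and 30.1 count as different and participants at 30.1 and 40 count as alike. The upper category spans 10 BMI units and the lower one 5. With no BMI quota, the two groups may also be very unequal in size.

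The Background of the article cites conflicting evidence on whether obesity alters the thermogenic response, and BMI is one of only two modifiers that section 4.9 names. If the difference between meals shifts gradually with BMI, a two-group comparison sees that trend with fewer effective participants than the trial has. A real trend could then be missed, or could hinge on who happens to fall just above 30.

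**Working it through.** **The plan's own figure.** The only relevant figure is the total of 30. It cannot be reproduced. Section 3.3 prints a "two-mean test formula for a quantitative trait in two independent groups" and sets error rates "with the alpha error set at 0.05 and the beta error at 0.2", but gives no means, SDs or attrition rate. The article gives no power or expected split for the BMI subgroups. What follows needs only n = 30, the eligibility range and the cut.

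**Measure of loss.** Suppose the within-person meal difference is linear in BMI. The share of information kept by the indicator BMI > 30 is then its squared correlation with BMI:

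r² = p(1 − p)(m₁ − m₀)² / Var(BMI)

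Here p is the proportion above 30, and m₁ and m₀ are the mean BMI above and below the cut. The loss is 1 − r².

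**Uniform BMI on 25-40 (assumed).**
- p = (40 − 30)/(40 − 25) = 2/3, so p(1 − p) = 2/9.
- m₁ − m₀ = 35 − 27.5 = 7.5.
- Var(BMI) = 15²/12 = 18.75.
- r² = (2/9)(56.25)/18.75 = 0.667, a loss of 33%.

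**Normal BMI truncated to 25-40 (assumed; mean and SD are those before truncation).**

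| Mean | r², SD 3 | Loss | r², SD 4 | Loss |
|---|---|---|---|---|
| 29 | 0.667 | 33% | 0.673 | 33% |
| 30 | 0.654 | 35% | 0.654 | 35% |
| 31 | 0.610 | 39% | 0.624 | 38% |
| 32 | 0.538 | 46% | 0.583 | 42% |
| 33 | 0.446 | 55% | 0.534 | 47% |

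The range over this grid is about 33-55%. In effective numbers, 30 × 0.667 = 20 participants and 30 × 0.446 = 13. Making up the loss would take 30/0.667 = 45 to 30/0.446 = 67 participants.

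Other shapes fall outside the range. A sample massed near 25 (truncated exponential, scale 4) loses 30%. A sample with few people below 30 (truncated normal, mean 34, SD 3) loses 65%.

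**Power for a linear trend.** Simulated at n = 30, two-sided 5%, without fat-free mass adjustment. Slopes and steps are in residual SDs of the within-person difference.

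| True effect | BMI distribution | Continuous | Two categories |
|---|---|---|---|
| Slope 0.5 SD per 4 BMI units | Uniform | 80% | 59% |
| Same slope | Truncated normal, mean 31, SD 4 | 57% | 39% |
| Half that slope | Uniform | 29% | 20% |
| Half that slope | Truncated normal, mean 31, SD 4 | 19% | 14% |
| Step of 1.1 SD at 30 | Uniform | 57% | 77% |

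The first slope is large: (0.5/4) × 15 = 1.9 SD across the eligible range. The last row shows the ranking reversing when the effect is a step at the cut.

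**The case against.** The strongest reply is that section 4.9 compares the two groups that define the trial's population, overweight and obese, at a cut not chosen from the data. The cited literature is framed in categories too. On that view a linear slope answers a question the plan does not ask, and the step scenario shows that two categories can be the better analysis. This stands in part. The loss is conditional on a roughly linear trend, and the categories have descriptive value. It does not make the cut the better main analysis, because nothing in the article gives a reason to expect the meal effect to jump at 30 and stay flat on either side.

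Four further limits stand:
- The BMI distribution is unknown, so no single loss can be attributed to this trial.
- The power figures of 80% versus 59% assume a large slope. At half that slope both analyses have little power, and keeping BMI continuous does not rescue the question.
- The calculations ignore the planned fat-free mass adjustment. The loss conditional on fat-free mass cannot be derived from the article.
- A condensed article may leave supplementary models to an analysis plan that is not shown. That would not alter the two-category comparison that section 4.9 states.

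A reader might infer that the cut weakens or biases the main result. The documents do not support that. The primary outcomes (sections 4 and 4.11.1) concern the meal contrast, which does not use the BMI categories, and section 3.3 does not size the trial for subgroups.

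**Conclusion.** The concern holds in a conditional form. Section 4.9 uses BMI only as two categories. For a roughly linear change in meal effect, this discards about 33% of the BMI information under uniform BMI, and about 33-55% under truncated normals with mean 29-33 and SD 3-4. Both distributions are assumptions, and samples further from the centre of the range can lose somewhat less or considerably more. A step at 30 would lose nothing and would favour the planned cut.

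The effect is confined to the efficiency of one secondary subgroup analysis. The point is worth acting on because the remedy is nearly free.

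**What to change.** In section 4.9, make the meal-by-BMI interaction with BMI continuous, in all 30 participants, the main BMI modifier analysis. Either regress each person's between-meal difference on BMI, or add a meal × BMI term to the mixed model already planned in section 4.7. Handle the fat-free mass adjustment as planned. Report the slope with a 95% CI, and plot the 30 within-person differences against BMI to check linearity. Keep 25-30 and >30 as a descriptive display.

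The cost is a sentence or two of analysis wording and one plot, with no new data. The downside is the assumed linear trend, which is less powerful than the two-category comparison if the effect is really a step at 30.

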### 4.10. Non-adherence and Missing Data

Since this study was conducted during an acute phase without follow-up, missing data was not anticipated except in unforeseen circumstances. If a participant was unable to complete the study on the scheduled day, an attempt was made to reschedule their evaluation. If rescheduling was not possible, the participant was excluded from the study and replaced by another eligible individual.

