##### 3.2.2.2. Exclusion Criteria

Exclusion criteria included: (1) Meal intolerance, (2) the occurrence of adverse health events during the study, (3) engaging in heavy physical activity during the study, (4) tobacco use during the study, (5) unwillingness to continue participation. 

Patient information was recorded, and eligible participants were contacted to receive a detailed explanation of the study plan. On the day of the visit, participants signed a standard written consent form. Those who declined to provide informed consent for any reason were not included in the study. 

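### Participants who cannot complete are excluded and replaced, possibly after randomisation and for meal-related reasons, although N = 30 already allows for attrition

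*Protocol article*

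**What the plan says.** Four parts of the protocol article bear on this.

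- **Section 4.10 (Non-adherence and Missing Data).** Rescheduling comes first: "If a participant was unable to complete the study on the scheduled day, an attempt was made to reschedule their evaluation". Failing that, "the participant was excluded from the study and replaced by another eligible individual". The section expects no missing data except in unforeseen circumstances.
- **Section 3.2.2.2 (Exclusion Criteria).** Items 1 and 2 read "1) Meal intolerance, (2) the occurrence of adverse health events during the study". Items 3 to 5 read "3) engaging in heavy physical activity during the study, (4) tobacco use during the study, (5) unwillingness to continue participation".
- **Section 4.1 (Allocation Sequence Generation).** Each participant draws a sealed envelope at baseline that fixes the meal order. Fifteen are allocated to each sequence.
- **Section 3.3 (Sample Size).** "To account for potential attrition, the final sample size was determined to be 30 participants".

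Section 4.7 names a generalized linear mixed model for the effects of time and meal. Section 3.4 says that the consent form covers how data are used if a participant withdraws. Section 3.6.3 says that the study was halted if complications arose. The article does not say whether data already collected from an excluded participant are analysed, or which sequence a replacement receives.

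**The concern.** In a crossover, the randomised comparison is protected only if leaving the analysis does not depend on how a person responded to a meal. Here some of the listed reasons for leaving could depend on it. The two meals differ widely in fat (45% against 15% of energy, Section 3.6), and satiety is a primary outcome (Sections 4 and 4.11.1). Someone who falls ill after one meal, or cannot tolerate it, may well have an unusual appetite response to it. If that person is taken out and a new one put in, the headcount returns to 30 but the randomised group does not. The analysis then describes people who got through both meals. The usual reason for replacement, protecting the sample size, is weak here because N already includes an allowance for loss.

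**Working it through.** **1. The plan's own figure.** The formula in Section 3.3 is n = (Z₁₋α/₂ + Z₁₋β)²(σ₁² + σ₂²)/(μ₁ − μ₂)², "with the alpha error set at 0.05 and the beta error at 0.2". The squared term is (1.960 + 0.842)² = 7.849 with unrounded quantiles. The article gives no means, standard deviations, pre-attrition n or attrition rate, so 30 can be neither reproduced nor refuted. The point does not depend on it.

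**2. Order of events.** The envelope is drawn at baseline, before the first meal. Adverse events, heavy activity and tobacco use are tied in the text to the study period. Unwillingness to continue implies having started. Intolerance of a study meal would ordinarily show once the meal is eaten. Section 4.10 covers failure to complete at either visit. So exclusion can follow randomisation, although it need not: someone who drops out before drawing an envelope can be replaced without harm.

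**3. Does replacement protect the planned size?** The attrition rate d is an assumption here, from 5% to 25%.

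- Completers left from 30 without replacement: m = 30(1 − d), rounded down.
- Number to randomise for 30 completers: 30/(1 − d), rounded up.
- Power with 30 completers if 80% was planned for m: Φ(√7.849 × √(30/m) − 1.960). Only the ratio 30/m enters, so this holds for paired or independent data.

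| d | m | Randomised to reach 30 | Power with 30 |
|---|---|---|---|
| 5% | 28 | 32 | 82.6% |
| 10% | 27 | 34 | 84.0% |
| 15% | 25 | 36 | 86.6% |
| 20% | 24 | 38 | 87.9% |
| 25% | 22 | 40 | 90.5% |

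Whatever rate was allowed for, 30 already leaves the intended number. Replacement buys power beyond the plan and changes who is analysed.

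**4. Selection, as an illustration only.** Suppose that a fraction d drops out, and that the tendency to drop out has correlation ρ with the within-person meal difference (bivariate normal). The completer mean then shifts by ρφ(z_d)/(1 − d), in SDs of that difference.

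- d = 5%, ρ = 0.3: 0.3 × 0.103/0.95 = 0.033.
- d = 20%, ρ = 0.5: 0.5 × 0.280/0.80 = 0.175.

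Both d and ρ are assumed and the direction is unknown. Adding people who also complete does not undo the shift.

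**The case against.** The case on the other side is substantial, and much of it stands.

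- **Replacement is narrower than it may seem.** A reader might infer that everyone with intolerance or an adverse event is replaced. Section 3.2.2.2 states exclusion only; Section 4.10 states replacement only after failed rescheduling. Joining them is reasonable, since such people do not complete, but it is a reading across sections.
- **Not every criterion is explicitly on-study.** Item 1 does not carry the words that tie items 2 to 4 to the study period. Food preferences and allergies were asked about at registration (Section 3.6.4), so item 1 could be a screening criterion.
- **Deletion of data is not stated.** A reader might infer it, but Section 3.4 says that the consent form addresses data after withdrawal, and that form is not shown.
- **Concealment of intolerance is not shown.** A CONSORT diagram is planned (Section 4) and a palatability questionnaire was used (Section 3.6.2). Either could reveal it.
- **Predictable allocation is a hypothesis.** A replacement might inherit the vacated sequence, but no section says so, and allocation is managed independently (Section 4.3).
- **The model is no cure.** A single session adds little to a within-person contrast. Someone with no data after a meal adds nothing to it. A mixed model does not remove bias when dropout depends on responses that were never observed.

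What remains is that the article states a rule of exclude and replace, that this rule can act after randomisation, and that the sample-size section makes it unnecessary.

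**Conclusion.** The concern holds in this limited form. Following Section 4.10 as written, together with Section 3.2.2.2, may leave an analysed set of people who completed both meals, selected after randomisation and partly for reasons that may relate to the meal. The allowance in Section 3.3 removes the need for replacement at any assumed attrition rate.

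The size of any bias cannot be derived from the article. The range of 0.03 to 0.18 SD of the within-person difference rests wholly on assumed dropout and correlation, and the true effect may be small, or nil if nobody left. It is tempting to set a shift in one meal's mean against the effect detectable with 30 pairs, but those are on different SD scales and the comparison should not be made. The conclusion assumes that item 1 refers to the study meals and that at least some exclusions follow the envelope draw.

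**What to change.** - **Analysis set.** State in Section 4.7 or 4.10 that all available data from every randomised participant enter the mixed model, under assigned sequence and meal received, as far as the consent described in Section 3.4 allows.
- **Replacement.** Replacements should not substitute for randomised participants. Anyone added after a post-randomisation withdrawal draws a new envelope and is analysed in addition to the original person.
- **Reporting.** Show exclusions, withdrawals and any replacements by meal, period and sequence in the CONSORT diagram, including people with no completed session. If nobody was replaced, one sentence saying so is enough.
- **Sensitivity.** Give a completers-only analysis alongside.
- **Reconcile the text.** Sections 3.2.2.2, 3.6.3 and 4.10 should agree on what happens to such participants and to their data. The rules for stopping a session need not change; the point concerns only the data.

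The cost is wording, a few incomplete records in the model, and possibly fewer than 30 complete pairs, which the attrition allowance was meant to absorb. The change can still be made after data collection if the records of excluded participants were kept.

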### 4.11. Expected Outcomes

#### 4.11.1. Primary Outcomes

The primary expected outcomes included the results of five indirect calorimetry measurements for each participant at each stage, as well as assessments of satiety conducted before the intervention, one hour after, and four hours after the intervention.

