**Results:**

The primary outcomes focused on the acute effects of the two dietary interventions on energy metabolism, particularly resting metabolic rate (RMR), and appetite response. Secondary outcomes included changes in lipid profiles, insulin, blood glucose levels, thyroid hormones, and epinephrine.

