## 2. Objectives

The primary objective of this study is to evaluate the effects of two distinct meal compositions—high-protein, high-fat, low-carbohydrate (HP-HF-LC) and high-protein, low-fat, high-carbohydrate (HP-LF-HC) meals—on appetite response (AR), RMR, diet-induced thermogenesis (DIT), and respiratory quotient (RQ) in adults aged 18 to 65.

The secondary objective is to assess the postprandial effects of HP-HF and HP-LF meals on blood glucose, low-density lipoprotein cholesterol (LDL-C), high-density lipoprotein cholesterol (HDL-C), triglycerides (TG), serum insulin, thyroid-stimulating hormone (TSH), thyroxine (T4), and epinephrine.

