## 4. Results

The CONSORT diagram was presented in Figure 3. As this article was a protocol study, it was anticipated that the diagram would be completed upon the study's conclusion. The primary outcome of this crossover trial was to investigate and compare the postprandial acute effects of two different meals on basal metabolic rate and satiety in overweight and obese men and women. The secondary outcome evaluated the impact of these meals on various blood markers, including blood glucose, LDL, HDL, total cholesterol (TC), TG, serum insulin, TSH, T4, and epinephrine.

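### The article defines its primary outcome in four different ways, and its stated alpha and power belong to a single variable that two of those definitions do not name

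*Protocol article*

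**What the plan says.** Four places in the protocol article state what is primary, and a fifth sets the sample size.

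- **Abstract, Results:** energy metabolism, "particularly resting metabolic rate (RMR), and appetite response".
- **Section 2, Objectives:** the primary objective is the effect of the meals "on appetite response (AR), RMR, diet-induced thermogenesis (DIT), and respiratory quotient (RQ").
- **Section 4, opening paragraph:** the comparison of "two different meals on basal metabolic rate and satiety in overweight and obese men and women".
- **Section 4.11.1:** "The primary expected outcomes included the results of five indirect calorimetry measurements for each participant at each stage", together with satiety before the meal and at one and four hours. No calorimetry variable, hour or summary is singled out.
- **Section 3.3, Sample Size:** "The respiratory exchange ratio was selected as the main variable, with the alpha error set at 0.05 and the beta error at 0.2".

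Section 4.7 (Data Management and Analysis) plans a repeated-measures mixed model with time and meal type as factors. It names no primary variable.

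**The concern.** These statements disagree in substance. Two name a pair of measures, one names four, and one names every calorimetry result without saying which variable is meant. The sample-size variable appears by name in only one of the four (as RQ, taking RQ and the respiratory exchange ratio as the same calorimetry ratio). The article's stated aim, in the Abstract's conclusions and in the Discussion, concerns resting energy expenditure, which is not the variable that the trial was sized on.

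Two things are at stake. With several definitions in print, a difference on RMR, DIT, RQ or appetite could later be presented as the primary result, and a reader could not tell a planned result from a selected one. In addition, the error rates in section 3.3 would be read as applying to the trial's main conclusion, although they were set for one variable only.

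**Working it through.** **1. The plan's own figure.** Section 3.3 gives two-sided alpha 0.05 (the formula uses Z at 1 − α/2), power 0.80 and a final size of 30. The 30 cannot be recomputed, because the article does not print the means, standard deviations, size before attrition or attrition rate. The steps below do not need them.

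**2. Number of measures in each definition.**

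| Place | Measures called primary | Respiratory ratio named? |
|---|---|---|
| Abstract, Results | 2 (RMR, appetite) | No |
| Section 2 | 4 (appetite, RMR, DIT, RQ) | Yes |
| Section 4, opening | 2 (basal metabolism, satiety) | No |
| Section 4.11.1 | not countable: all calorimetry results, plus satiety | Not by name |
| Section 3.3 (sample size) | 1 (respiratory exchange ratio) | Yes |

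**3. False-positive rate under stated assumptions.** Assume that each of k measures is tested at 0.05 without adjustment, that any one significant result counts as success, and that there is no true difference. Under independence the rate is 1 − (1 − 0.05)^k:

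- k = 1: 5%
- k = 2: 1 − 0.95² = 0.0975
- k = 4: 1 − 0.95⁴ = 0.185

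For jointly normal test statistics, independence is the worst case. The documents give no correlations, so a range is shown, from a simulation of 1,000,000 draws of equally correlated two-sided z-tests:

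| Common correlation | k = 2 | k = 4 |
|---|---|---|
| 0 (exact) | 9.75% | 18.5% |
| 0.5 | 9.0% | 15.5% |
| 0.7 | 8.3% | 13.0% |
| 0.9 | 7.0% | 9.4% |

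**4. Cost in power if four measures stay primary with adjustment.** The design effect is the one that gives 80% power at 0.05, so its standardised size is 1.960 + 0.842 = 2.802. Holm's first step over four measures is 0.05/4 = 0.0125, with critical value 2.498. Power at that step is Φ(2.802 − 2.498) = Φ(0.304) = 0.62. To restore 80% there, the sample size would need a factor of ((2.498 + 0.842)/2.802)² = 1.42, which takes 30 to about 43.

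**The case against.** The strongest reply is that the article nowhere says that each measure will be tested at 0.05. That level appears only in section 3.3. No success rule is given, and if all the primary measures had to be significant there would be no inflation. A multiplicity rule may stand in an analysis plan or full protocol that is not shown, so its absence here is not a fault. All of this stands, and it is why the rates above are conditional.

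It is also fair to say that the definitions share two domains, calorimetry and appetite, and that the fasting reading listed in section 4.11.1 is needed as the baseline for post-meal change. DIT is ordinarily derived from the same energy-expenditure readings as RMR, so the four measures are unlikely to be independent.

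A reader might infer that the trial has a false-positive rate of 13–19%. The documents do not support that. Only the Objectives list four measures, and the lower end needs an assumed correlation of about 0.7 that no section supplies. Nor do they support counting every post-meal hour as a separate test, since section 4.7 plans a repeated-measures mixed model.

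The objection does not remove the contradiction itself. An unseen analysis plan could add a multiplicity rule, but it could not make these five places agree.

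**Conclusion.** The point holds as an inconsistency in the primary outcome, with a conditional consequence for the error rate. Sections 2, 4 (opening) and 4.11.1 and the Abstract do not define the same primary outcome. The alpha and power in section 3.3 attach to a variable that two of those four places leave out.

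Under unadjusted testing at 0.05 and an any-one-significant rule, the false-positive rate would be at most 9.75% for the two-measure definitions and at most 18.5% for the four-measure one, falling to about 7% and 9% at a correlation of 0.9. Every such scenario exceeds 5%, but none is stated as the plan. The need to reconcile the definitions does not depend on which scenario applies, and correcting the sample-size formula would not remove it.

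**What to change.** Bring the Abstract, section 2, section 3.3, the opening of section 4 and section 4.11.1 into agreement on one primary variable, with one baseline-corrected post-meal summary per participant per visit. The 4-hour incremental area, measured from the same visit's fasting value, is one example. Make the other calorimetry and appetite measures secondary.

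State in section 3.3 which variable the 80% power applies to. If the primary is the respiratory exchange ratio, the existing basis can be cited. If it is RMR, in line with the stated aim, section 3.3 should say that the calculation was made for a different variable.

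If several measures stay primary, apply Holm across them and state that 80% power is then not guaranteed for any of them; with four, it is about 62% at the design effect at the first step.

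The trial was registered retrospectively (section 3.2.1) and much of the article is in the past tense, so timing matters. The choice should be made before comparative results are examined, or be labelled as made afterwards.

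The edit is confined to wording. The real cost is that some measures lose primary status, or face a stricter threshold if kept.
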